**Figure 1 F1:**
[figure not shown]
Overview of the prevention of dementia using mobile phone applications (PRODEMOS) platform and its functionalities. Main features of coach portal: viewing and adjusting details of goals and measurements; sending and receiving chat messages to and from the participants; sending education and news items. Main features of intervention app: setting and adjusting goals; entering measurements; sending and receiving chat messages to and from the coach; reading education and news items automatically pushed by platform or received from the coach; receiving periodic adverse event questionnaires and self-assessment questionnaires. Main features of assessor portal: blinded collection of participant data through electronic case report forms and questionnaires. The control application has similar connections with the assessor portal and the researcher portal/database, but is not connected to the coach portal.

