Participants have only access to one of two versions of the participant app. Participants randomised to the intervention condition will have access to an interactive smartphone application in their own language (English in the UK and Mandarin in China). The intervention app facilitates coach-supported self-management of seven dementia risk factors, including overweight, unhealthy diet, insufficient physical activity, smoking, hypertension, dyslipidaemia and diabetes. Participants can set personal goals for lifestyle change, following the specific, measurable, achievable, realistic and time-bound principle. Participants receive automated reminders to enter measurements (eg, number of steps and blood pressure) for these goals, facilitating progress monitoring. The intervention participants will receive support from an experienced lifestyle coach, who is trained in motivational interviewing and works according to a coach protocol based on current guidelines for risk factor management. Regular training sessions in each country will enhance uniformity in coaching procedures, taking cultural differences into account. During the baseline visit, after randomisation, the coach discusses the participant’s dementia risk profile, and a first lifestyle goal will be set through the app. After the baseline visit, all communication between the participant and coach will take place through the messaging functionality. Through the coach portal, the coach can view goals and measurements, send tailored education modules, and offer remote support to facilitate sustainable behaviour change.

Participants randomised to the control condition will have access to the control app, which is similar in appearance but only contains education material, lacking interactive features and coach-support. During the baseline visit, control participants will receive concise feedback on their risk profile.

The PRODEMOS intervention in its current design is positioned as add-on to existing care.

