The baseline visit will be conducted face-to-face by the health coach at the GP practice or local community venue. During this visit, self-assessment questionnaires are reviewed, relevant medical history and medication use are recorded, and participants are randomly assigned to one of the treatment conditions. Only intervention participants will set a first lifestyle goal together with the coach, according to their dementia risk profile.

All participants will receive periodic adverse event (AE) questionnaires in the app, assessing incident dementia, MCI, CVD and diabetes. All self-reported outcomes will be verified with the participant’s treating physician.

After 18 months, the questionnaires and all measurements performed during the screening and baseline visit are repeated during the final visit.

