#### Data analysis

The effect on the CAIDE Score will be analysed using linear mixed-effect models according to the intention-to-treat principle, taking clustering within partner pairs and country into account by testing best fit for random intercept and/or slope. If needed, we will adjust for baseline imbalances and take clustering of the intervention within centre and/or coach into account. No imputation of the CAIDE Score will be done for the primary analysis. In sensitivity analyses, we will use multiple imputation to assess the impact of missing items needed to calculate the CAIDE Score, provided there are no indications that the variables are missing not at random, and a per-protocol analysis for those adherent to the intervention will be performed. Moreover, we will explore the interaction of intervention duration with the effect of the invention by adding an interaction term (intervention duration*randomisation group) to the main model. This will give insight into the potential additional intervention effect in participants with a follow-up time of less than 18 months.

Subgroup analyses will be performed for country, sex, age group, having a history of CVD, number of risk factors, willingness to change lifestyle (assessed with one question during the baseline visit), participation with(out) a participating partner, having the same coach during the full length of the study and the number of goals set. For all these factors, interaction terms will be included to test for between-subgroup differences in intervention effects.

The effect on individual modifiable components of the CAIDE Score and 10-year CVD Risk Scores will be analysed using linear mixed-effect models according to the intention-to-treat principle, taking clustering within partner pairs and country into account. Self-assessment scales, which are mostly ordinal, will be regarded as linear scales if there are at least four categories and the ‘distance’ between the categories can be regarded equal. Poisson regression or zero-inflated models may be applied to distributions resembling count or zero-inflated data. The choice of the final model will be a compromise between optimal fit and interpretability of the results for a general clinical public.

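### Two of the nine subgroup factors (same coach throughout, number of goals set) exist only in the intervention arm after randomisation, so the promised interaction tests cannot be estimated

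*Protocol article*

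**What the plan says.** The subgroup paragraph under Data analysis names nine factors: country, sex, age group, history of CVD, number of risk factors, willingness to change lifestyle, partner participation, and finally "having the same coach during the full length of the study and the number of goals set". The next sentence makes no exception: "For all these factors, interaction terms will be included to test for between-subgroup differences in intervention effects".

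Elsewhere the article states who has goals and a coach:

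- Intervention and control condition: the control app "only contains education material, lacking interactive features and coach-support". The caption of Figure 1 adds that it "is not connected to the coach portal".
- Study logistics and data collection: "Only intervention participants will set a first lifestyle goal together with the coach, according to their dementia risk profile".
- Intervention and control condition: "The intervention participants will receive support from an experienced lifestyle coach". On timing: "During the baseline visit, after randomisation, the coach discusses the participant’s dementia risk profile", and the first goal is set at that point.
- Under Primary and secondary outcomes, data on goals set are also among the user statistics for adoption, which is an implementation outcome.

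**The concern.** A test of effect modification asks whether the randomised contrast differs between levels of a factor. For that, the factor must take its levels in both arms and should not be a consequence of allocation. Neither holds for these two. The number of goals is behaviour under the intervention, and coach continuity is known only when follow-up ends. Neither has a counterpart among controls.

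An analyst who follows the text literally will find that the term drops out of the model. The likely next step is to split the intervention arm by level and set each part against all controls, and to report the result as a subgroup effect. In a hybrid effectiveness–implementation trial, a statement that the app works better in people who set more goals would be read as guidance for roll-out. The design cannot support that statement.

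**Working it through.** **1. The plan's own figures.** The target difference under Sample size is 0.290 − 0.104 = 0.186 CAIDE points. The two SDs of change (1.47 and 1.36) give a common SD of √((1.47² + 1.36²)/2) = 1.416. With 80% power and two-sided 0.05, n per arm = 2 × 1.416² × (1.960 + 0.842)² / 0.186² ≈ 910, or 1820 in total. Then 1820/0.79 = 2304, close to the stated 2319. The sample size is not in question; 0.186 serves only as a yardstick below.

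**2. Estimability.** Let A be arm (1 = intervention, 0 = control) and F the factor, with F = c for every control. The model has the columns 1, A, F and A×F. In the intervention arm A×F = F; in controls A×F = 0. Hence, for every participant,

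A×F = F − c + c×A.

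The fourth column is an exact combination of the first three, whatever c is. A numerical check with c = 0 gave rank 3 of 4 for goals set and 3 of 4 for same coach. A baseline factor such as sex gave 4 of 4. If F is missing in controls, their rows drop out, A is constant, and no treatment contrast is left.

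**3. What a workaround estimates.** A three-group coding (control, intervention low, intervention high) is full rank. The difference between its two effects is (high − control) − (low − control) = high − low. The controls cancel, so the supposed interaction is a within-arm comparison of people who behaved differently.

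**4. Size of the bias, simple form.** Suppose there is no treatment effect, a share p of the arm is engaged, and engaged people would improve by g points more than the rest in either arm. The controls are a mixture of both kinds, so engaged participants against all controls show g × (1 − p), and the rest show −g × p. Both g and p are assumptions; the article gives neither.

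| Assumed gap g | Spurious effect, p = 1/2 | Spurious effect, p = 2/3 |
|---|---|---|
| 0.1 | 0.05 | 0.033 |
| 0.2 | 0.10 | 0.067 |
| 0.4 | 0.20 | 0.133 |

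The value p = 2/3 matches the pilot, where 10 of 15 intervention participants set at least one goal. At p = 1/2, the spurious effect reaches 0.186 only if g = 0.186/0.5 = 0.372.

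**5. Size of the bias, simulated.** Each arm had 948 completers (2400 × 0.79 / 2), with SD 1.416 and the same true effect of −0.186 in everyone. Latent motivation has correlation r with improvement in both arms and r_g with goals set. The intervention arm is split at the median number of goals, and each half is compared with all controls. The correlations are assumptions.

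| r | r_g | More goals | Fewer goals | False difference between halves |
|---|---|---|---|---|
| 0 | 0.3 to 0.7 | about −0.19 | about −0.19 | about 5% |
| 0.1 | 0.3 | −0.222 | −0.154 | 11% |
| 0.2 | 0.5 | −0.300 | −0.076 | 68% |
| 0.3 | 0.7 | −0.427 | +0.049 | 100% |

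The shift has the closed form 1.416 × r × r_g × √(2/π). For r = 0.2 and r_g = 0.5 it is 1.416 × 0.1 × 0.798 = 0.113, which agrees with the simulated −0.300 and −0.076 around −0.186.

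**6. Coach continuity.** No bias figure is given, because its direction and size depend on why a coach changed. Staff turnover may be nearly unrelated to prognosis. Early dropout, or the 12-month end of the permitted 12 to 18 months (Protocol adjustments due to COVID-19 pandemic), makes an unchanged coach more likely and could link the factor to outcome.

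**The case against.** Four points can be made on the other side.

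- *Controls do meet a coach.* The article says "The baseline visit will be conducted face-to-face by the health coach at the GP practice or local community venue", and this covers both arms. But controls then receive only brief feedback and have no coach support afterwards. Continuity over follow-up is undefined for them or the same for all, so the algebra is unchanged.
- *The full analysis plan is separate.* The article says that the plan, with the subgroup hypotheses, is on the registry website. It may restrict these two factors to the intervention arm. That limits how sure one can be that the faulty model will be run. It does not rescue the sentence in the article, which states an interaction test for every factor; no added hypothesis makes these two estimable.
- *Not estimable does not mean not analysable.* This stands. The failure concerns the arm-by-factor term. The within-arm association can be estimated, and causal methods such as principal stratification could be used with stated assumptions. The difficulty with those analyses is interpretation.
- *The damage is limited.* This also stands. Two of nine subgroup factors are affected, and software will usually warn about or drop an aliased term.

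A reader might go further and infer that every comparison by level is biased. The documents do not support that: bias needs a link between level and prognosis, the simulation shows none at r = 0, and coach turnover may have no such link.

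**Conclusion.** The article states an analysis that cannot be carried out for two of its nine subgroup factors. This follows from its own account of the two arms and rests on no outside assumption. The further point, that comparing one level with all controls is open to bias, holds whenever the level is related to prognosis. That is plausible for goals set; for coach continuity it depends on the reason for the change.

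The size is not known. On the assumed gaps of 0.1 to 0.4 points with half the arm engaged, the spurious effect runs from 0.05 to 0.20. A reader might take 0.20 as showing that the bias exceeds the 0.186 target. It does so only at a gap above 0.372, twice the target itself, and nothing in the documents fixes that gap.

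Nor should a reader infer that the trial's main result is at risk. The primary intention-to-treat analysis, the sample size and the other seven subgroup factors are untouched. This is a point that should be fixed, not one that stops the plan.

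**What to change.** Remove coach continuity and number of goals from the list of factors tested by interaction. Report both within the intervention arm only, as descriptive associations labelled non-causal, beside the adoption outcomes where goals set already appear. Keep interaction tests for factors fixed before randomisation.

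The question on willingness to change lifestyle can stay in the list, since it is asked at the baseline visit and randomisation follows the baseline assessments. It should not be presented as a validated stand-in for engagement: it is a single question, and the article gives no evidence on that use.

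If the investigators want a causal statement about engagement, they would need a method such as principal stratification or a complier-average effect, with its assumptions written down in advance.

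The cost is one sentence in the analysis section. No data collection or sample size changes.

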**Secondary outcomes**	
Individual modifiable components of the CAIDE score†	Estimated 10-year cardiovascular risk
Number of uncontrolled risk factors	LIBRA dementia risk score
Active smoking	Number of hospital admissions
Medication adherence	Diet‡
Number of drugs	Disability§
Incident dementia¶	Anxiety**
Incident MCI¶	Self-management††
Incident cardiovascular disease¶,§§	Depressive symptoms‡‡
Incident diabetes¶	Quality of life¶¶
All-cause mortality	Cost-effectiveness

*Assessed according to WHO standard for physical activity of at least 150 min per week.

†Physical activity assessed with the International Physical Activity Questionnaire—Short Form.

‡Assessed with Short-Form Food Frequency Questionnaire (UK) and China Kadoorie Biobank Food Frequency Questionnaire (China).

§Assessed with the WHO Disability Assessment Schedule.

¶Self-reported and cross-checked with general practitioner file.

**Assessed with the Hospital Anxiety and Depression Scale—Anxiety.

††Assessed with the Partners In Health.

‡‡Assessed with the Geriatric Depression Scale.

§§Defined as myocardial infarction or stroke.

¶¶Assessed with the ICEpop CAPability Measure for Adults and EuroQol Five Dimensions Three Levels.

BMI, Body Mass Index; CAIDE, Cardiovascular Risk Factors, Ageing and Incidence of Dementia; LIBRA, Lifestyle for Brain Health; MCI, mild cognitive impairment.

Implementation outcomes include acceptability, adoption, appropriateness, feasibility, fidelity, coverage, sustainability and costs of the implementation. User statistics, including data on goals set, messages sent and education items read, will be analysed to assess adoption and sustained use of the platform. In-depth interviews with participants and coaches will focus on user experiences, particularly with respect to barriers and facilitators for (sustained) platform use. All implementation outcomes and evaluation methods are shown in table 2.

**Table 2 T2:** Summary of implementation research methods and outcomes

Method	Outcome	Measurement	Population*	Timing of assessment
Quantitative	Coverage	(Non)Response rates, comparison characteristics of participants with eligible population	Potential target population	At baseline
	Adoption	Utilisation, usage, and uptake	Intervention participants, coaches	After 2 weeks
	Appropriateness	Short questionnaire of perceived fit or relevance in the target population and the coaches	Intervention participants, coaches	After 3 months and at study end

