### Statistical analysis

#### Sample size

The CAIDE Score will be used as primary effectiveness outcome. We decided to use a difference of 0.186 points on the CAIDE Score between the average of both study groups as a minimum target threshold, because this difference was observed in the Prevention of Dementia by Intensive Vascular Care trial after 2 years (p=0.005; intervention group=−0.290±1.47 SD and control group=−0.104±1.36 SD). Attrition after 2 years of follow-up was 21% in this study.^14^ With 80% power, a 0.05 two-sided significance level, accounting for 21% attrition, and a mean difference in change in CAIDE of 0.186, the required sample size is estimated to be 2319 participants. To allow for unexpected factors, we raised this to 2400.

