Prevalence ratios will be used for self-assessment instruments with defined cut-offs for the presence or absence of a condition, for example, ‘depressive symptoms’ for a GDS >5. For (clinical) dichotomous outcomes, such as incident CVD, dementia or mortality, Cox proportional hazard models will be used with time using baseline as timescale. A sensitivity analysis will be performed using age as timescale.

The full analysis plan, including the health economic analysis plan entailing the cost–consequence analysis of the within-trial results, the cost-effectiveness analyses and the cost–utility analysis and hypotheses for the subgroup analyses, is published on the ISRCTN website: http://www.isrctn.com/ISRCTN15986016.

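### The plan commits depressive symptoms on the GDS to a yes/no analysis, although the score may also qualify for the linear-scale rule, and does not say which analysis is the main one

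*Protocol article*

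**What the plan says.** All of the analysis rules below are in the protocol article, Statistical analysis, Data analysis.

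- **Linear rule.** "Self-assessment scales, which are mostly ordinal, will be regarded as linear scales if there are at least four categories". A second condition follows: the distances between categories must be regarded as equal.
- **Count rule.** "Poisson regression or zero-inflated models may be applied to distributions resembling count or zero-inflated data".
- **Choice of model.** "The choice of the final model will be a compromise between optimal fit and interpretability of the results for a general clinical public".
- **Cut-off rule, in the next paragraph.** "Prevalence ratios will be used for self-assessment instruments with defined cut-offs for the presence or absence of a condition". The example is "depressive symptoms’ for a GDS >5".
- **The outcome.** Table 1 has a single secondary entry for depressive symptoms, footnoted "Assessed with the Geriatric Depression Scale".
- **Where the detail is said to be.** The section closes by pointing to the registry website: "The full analysis plan, including the health economic analysis plan". That plan is not among the documents reviewed.

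**The concern.** A score that can be cut at >5 takes at least seven values (0 to 6), so the GDS meets the category-count condition of the linear rule. Whether it meets the equal-spacing condition is left to judgement. The same instrument is also the named example under the cut-off rule, and the article gives no order of precedence.

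There are three ways to read this:

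1. The specific rule governs. This is the most natural reading. The plan has then committed a multi-level score to a yes/no analysis. A participant who moves from 14 to 7 counts as unchanged, while one who moves from 6 to 5 counts as no longer having the condition.
2. Both analyses are reported. One secondary outcome then has two results and neither is designated as the main one.
3. The analyst chooses by fit and interpretability. That choice can depend partly on the data.

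What is at stake is the precision of one secondary result and clarity about which result counts.

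**Working it through.** **Inputs from the protocol article.** Planned total 2400, attrition 21%, two-sided 5% level, 80% power and CAIDE change SDs of 1.47 and 1.36 (Sample size: "With 80% power, a 0.05 two-sided significance level, accounting for 21% attrition"); 1:1 allocation (Randomisation and blinding). The article gives no GDS prevalence, mean, SD or number of items, so those are assumptions below.

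**Step 1. The plan's only design figure.** It concerns CAIDE, not the GDS. The pooled SD is sqrt((1.47² + 1.36²)/2) = 1.416. A difference of 0.186 then needs 910 per arm, or 1820 in total, and 1820/0.79 = 2304. The stated figure is 2319, which is 0.6% away, so it reproduces. It is used here only to set the number analysed: 2400 × 0.79 / 2 = 948 per arm.

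**Step 2. Information kept when a normal score is cut.** Let p be the proportion above the cut-off and c the normal quantile at 1 − p. Relative to comparing means, the information kept is φ(c)² / [p(1 − p)].

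| p (assumed) | φ(c) | Kept | Lost |
|---|---|---|---|
| 5% | 0.103 | 0.224 | 78% |
| 10% | 0.175 | 0.342 | 66% |
| 20% | 0.280 | 0.490 | 51% |
| 33% | 0.362 | 0.593 | 41% |
| 50% | 0.399 | 0.637 | 36% |

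**Step 3. Skewed discrete scores.** A GDS score may be skewed, so the comparison was repeated with beta-binomial and truncated negative binomial scores on an assumed 0-15 range. Mean parameters were 2 to 5 in controls and 10% lower in the intervention arm. Write m, v and q for the mean, variance and proportion above 5, with subscripts for the two arms. The information kept is

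[(q0 − q1)² / (q0(1 − q0) + q1(1 − q1))] ÷ [(m0 − m1)² / (v0 + v1)].

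The proportion above 5 ran from 6% to 41%, and the loss from 28% to 65%. The largest loss was in a beta-binomial score with mean 2 (9.8% above 5, loss 65.1%). The smallest was in a negative binomial score with mean parameter 5 (29.7% above 5, loss 27.9%).

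**Step 4. Illustration as power.** The standardised difference that a comparison of means detects with 80% power is (1.960 + 0.842) × sqrt(2/948) = 0.129. Shift a normal score by that amount, cut it, and compare the two proportions. Power is Φ(difference/SE − 1.960).

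| Controls above cut | Intervention above cut | Difference/SE | Power |
|---|---|---|---|
| 10% | 7.9% | 1.58 | 35% |
| 20% | 16.6% | 1.92 | 48% |
| 33% | 28.5% | 2.13 | 57% |
| 50% | 44.9% | 2.24 | 61% |

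Steps 2 to 4 ignore baseline adjustment and partner clustering. They compare two ways of using the same score and do not predict the trial's power.

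**The case against.** The strongest case against the point has four parts.

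- **There is no contradiction.** The linear rule is general and conditional, and it never names the GDS. The cut-off rule is specific and does name it. A reader might infer that the article defines one outcome in two incompatible ways, but the text does not support that: it never assigns the GDS to a linear analysis. This stands. What remains is an overlap without a stated order and, on the natural reading, an inefficient choice.
- **The detail belongs in the full analysis plan.** That plan may well settle the order for each instrument. This stands in part: silence on precedence alone would not be a finding. The article does, however, state a rule and name the instrument, and that choice can be assessed.
- **The size is assumed.** This stands. A reader might take one band, such as 40-65%, as the loss. That band needs a normal score and roughly 10-33% above the cut-off, neither of which is in the article. Nor does the cut generally remove most of the power: among the cases in Step 4, only 10% prevalence more than halves it.
- **A clinical cut-off is a legitimate preference, and the outcome is minor.** Depressive symptoms is one of about 20 entries among the secondary outcomes in Table 1. It is not named among the main secondary outcomes in the text, and it lies outside the sample-size calculation. This stands and sets the severity.

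Two further inferences should be resisted. A clear mean difference beside an inconclusive prevalence ratio would reflect different precision, not opposite conclusions. And the article states a self-assessment cut-off for no instrument other than the GDS, so it does not show that other scales are affected.

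**Conclusion.** The point holds as a minor one. The article commits cut-off instruments, with the GDS as the only one named, to a prevalence ratio. The GDS score could qualify for the linear rule if equal spacing is accepted, or for the count models, and the article does not say which analysis is the main one for depressive symptoms.

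Dichotomising cost a substantial share of the information in every scenario computed: about 36-78% for a normal score with 50% down to 5% above the cut-off, and about 28-65% for skewed scores. The direction of the loss is consistent across these scenarios. Its size depends on an unknown prevalence and distribution and should be quoted only as a range. The 80% starting power in the illustration is a reference level chosen for the comparison; the trial claims none for this outcome. Neither the primary analysis nor the sample size is affected.

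**What to change.** In Data analysis, add a sentence that sets the order. For the GDS, and for any other cut-off instrument that meets the linear or count rule, the main analysis is the 18-month score adjusted for its baseline value, using the linear or count model already allowed. The prevalence ratio is then reported as a supportive presentation of the same outcome. If the full analysis plan on the registry website already sets an order, the two texts should be aligned.

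The cost is one sentence and no new data, because the questionnaires are completed before randomisation and repeated at the final visit. The small downside is that a mean difference is less directly interpretable to clinicians than the presence or absence of a condition, and keeping the prevalence ratio alongside it offsets this.
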